### Incentives for GPs, practices and Networks

GPs participating in two facilitated peer group clinical meetings and undertaking a review of their patients are eligible for mandatory continuing professional development points recognised by the Royal Australian College of General Practice and the Australian College of Rural and Remote Medicine. This quality prescribing initiative also makes the practice eligible for payment as part of the Australian Government’s Practice Incentives Program.

The funds provided to the Networks to deliver the project were deliberately weighted to ensure Networks recruited and retained the required minimum number of practices for the duration of the project. Networks were requested to provide $A500 to each practice to assist with data cleaning processes at the project start.

### Recruitment procedures

Recruitment of GP practices occurred in two stages. In stage 1, Networks were recruited through a call for Expressions of Interest from NPS and AGPN to recruit practices and deliver the intervention. In stage 2, Networks recruited practices and GPs to participate in the study and employed project facilitators to deliver and co-ordinate the intervention in participating practices in their Network.

### Project facilitator training

Two 2-day facilitator training workshops were delivered by NPS at the study start to give project facilitators a clear understanding of the Project, its aims, their roles and responsibilities and principles of research design, privacy issues and project implementation. Clinical knowledge of management of patients with HT and CHF was another important component. The focus then turned to developing skills in communication, negotiation and persuasion, group facilitation, problem solving, facilitating decision making, and change management. Data management skills covered demonstration of the software installation, data collection and cleaning, data transfer and storage and data interpretation as well as hands on use of the data extraction tool and practical examples on how to improve data quality. On-going monthly teleconferences with groups of facilitators were also established to support facilitators in the field.

### Data Extraction and data cleaning

A third party software tool was used to extract prescribing data from general practices. The tool was developed to: (1) provide *clinical indicator reports* to measure the clinical indicators; (2) provide *data quality reports* to identify missing or incorrect clinical data to ensure accurate calculation of clinical indicator reports; and (3) enable *data extracts* at baseline, and at regular intervals through the intervention, in order to evaluate changes in prescribing over the intervention period. The data extraction tool was developed over a period of 18 months and included functional specification development, software development, testing and piloting in general practice. The functional specifications included definitions for where data is stored in clinical software; how the data is coded or recorded, and the algorithms for calculating the clinical indicator.

A pre-intervention phase of two months included the installation of the data extraction software, training of practice staff in its use for data cleaning, upload and transfer (see Additional file 4:Appendix 4). Data quality reports obtained from the data software extraction tool allowed the practice to *clean* their data by improving the quality of coding and completeness of fields in the practice clinical software during these first two months.

Clinical indicator reports were collected from the GP clinical software just before the initial clinical meeting and every quarter. They were used within the practices to give individual GP and practice-level feedback. Evaluation data extracts retrieved anonymised data for patients with relevant conditions. This complete data subset with intervention-relevant variables extracted was transferred to a secure data repository located at NPS for the impact evaluation.

### Data Analysis

The unit of randomisation is the practice and unit of analysis is the patients accounting for clustering by practice (using *Proc surveyfreq* in SAS Enterprise Guide v4). The following analysis will be presented comparing the three groups:

a. Successive cross-sectional analyses at six-month intervals which include any practice with patient data available at each point. This will be to estimate point prevalences of each indicator before and after the intervention. Comparisons of practice proportions of patients meeting the individual guideline-recommended indicators (with 95% confidence intervals) across intervention groups will be conducted using χ^2^ statistics.

b. Longitudinal (cohort) estimates of changes in indicators occurring between time points, based on data from patients who had at least one visit before baseline and at least one visit following the intervention.

c. Sequential indicators will be calculated where changes in prescribing behaviours are measured only for patients not meeting guideline-driven indicators in the preceding 6-12-month period (e.g. proportion of CHF patients using an ACE inhibitor or angiotensin II-receptor antagonist at 6 months, out of those not receiving this treatment at baseline). This approach will show whether the intervention modified prescribing behaviour using a denominator where patients have scope for improvement.

Changes in the proportion of patients appropriately prescribed target medicines before and after the intervention will also be presented, with χ^2^ statistics for categorical measures (e.g. on heart failure medication or not at each time point), and significance testing of before and after the intervention effects within intervention groups based on paired t tests for continuous measures (e.g. mean blood pressure change) within groups and with a p-level of ≤0.01 considered to be statistically significant.

Supplementary regression analyses of the cohort will identify predictors of improved prescribing at 12 and 18 months after controlling for other possible confounders (determinants at the practice level) such as practice size, rural/urban location, socio-economic level of the area, percentage female doctors, mean years of GP experience. Post-test comparisons will be conducted between the intervention and wait-control arms using intention to treat analysis [55] and models that account for the non-independence of observations due to the clustering of practices in a Network and clustering of patients within practices and GPs. Separate binary logistic regression models will be analysed for CHF and HT adjusting for clustering effects of practice and GP [56]. Stepwise regression techniques will be used. Odds ratios will be used as the common measure of the estimated effect of the intervention and the independent effect of explanatory variables. To account for chance imbalance across intervention groups,[57] explanatory variables for each model will include patient characteristics, practice characteristics, and location of the Network. The researchers analysing the impact of the intervention on study outcomes have no contact with Networks or practices involved and are blinded to allocation group code at the baseline analysis stage.

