**Figure 1 F1:**
[figure not shown]
Quality improvement intervention process.

Identification of patients suitable for clinical review occurred after the initial clinical meeting (step 3). A follow-up facilitated peer group clinical meeting was held around two to three months after the first meeting (step 4) to check progress on the patients prioritised for review of therapy and any changes to the prescribing data feedback.

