### Study groups and randomisation

Practices agreeing to participate were registered and randomly allocated automatically into one of the three study groups (either into one of the two intervention groups or into the wait-control group) using computer generated random numbers. Block randomisation was used to enable balanced representation of practices in each of the Networks. The randomisation determined the sequence of exposure to the intervention as follows (see Figure 2):

Group 1 received the intervention for the CHF topic in the first six months and the HT topic in the next six months. In the first six months, this group also acts as the topic control group for group 2.

Group 2 received the intervention for the HT topic in the first six months and the CHF in the next six months and also acts as topic control group for group 1 in the first six months.

Group 3 is a wait-control for groups 1 and 2 in the first six months and did not receive any intervention in the first six months. This group received the intervention after six months and implemented the 2 topics sequentially – the order of topics was left up to the practice involved to choose. This group acts as ‘true’ control for groups 1 and 2 in the first six months.

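### Cohort analysis (b) selects patients on a visit after randomisation that the intervention can influence and that has no stated anchor date in the wait-control group

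*Protocol article*

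**What the plan says.** The Data Analysis section lists three analyses that compare the groups:

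- (a) Cross-sections every six months, which "include any practice with patient data available at each point".
- (b) Longitudinal estimates of change, "based on data from patients who had at least one visit before baseline and at least one visit following the intervention".
- (c) Sequential indicators, "measured only for patients not meeting guideline-driven indicators in the preceding 6-12-month period". The worked example is CHF patients on an ACE inhibitor or angiotensin II-receptor antagonist at 6 months, "out of those not receiving this treatment at baseline".

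The same section also plans before-and-after tests within groups and supplementary regressions of the cohort at 12 and 18 months. It then states: "Post-test comparisons will be conducted between the intervention and wait-control arms using intention to treat analysis". The Discussion speaks of analysing the patients of all GPs in a practice, including GPs who did not take part.

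Three other places bear on this:

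- The text after Figure 1 says: "Identification of patients suitable for clinical review occurred after the initial clinical meeting (step 3"). The second meeting then checks progress on those patients.
- Under Study groups and randomisation, Group 3 "did not receive any intervention in the first six months". The Discussion confirms that the wait-control comparison covers only that period.
- The sample size section expects 40-50% of practices to drop out and plans for absolute increases of 10 points (ACE inhibitors) and 15 points (beta blockers).

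**The concern.** Randomisation protects a comparison of everyone allocated, or of a set fixed before the intervention could act. Analysis (b) is neither, because entry depends on a later visit. In Groups 1 and 2 that visit may be prompted by the review step for the allocated topic, and Group 3 has no such step in the first six months. A visit after the intervention also has no evident date in a group that has not yet had one, so the rule cannot be applied alike in every group as written. The cohort could then differ between groups in who is counted as well as in how they were treated.

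Analysis (a) has a separate weakness. Its before and after prevalences can come from different practices, and heavy practice loss is expected. Part of an apparent change could reflect which practices remained.

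**Working it through.** **Expected practice loss.** The article gives 99 practices before drop-out and at least 180 after. 99/(1-0.40) = 165, 99/(1-0.45) = 180 and 99/(1-0.50) = 198, so 180 corresponds to 45% loss. With 40-50% loss, 108 to 90 of 180 practices would remain.

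**Analysis (b).** The article gives no visit rates or baseline prescribing rate, so these inputs are assumed: 60% of CHF patients treated at baseline, and 75% of all patients making a later visit, except that review raises this to 95% among untreated patients in the intervention arm. Per 100 patients:

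- Control cohort: 60×0.75 = 45 treated and 40×0.75 = 30 untreated, so 45/75 = 60.0% treated at baseline.
- Intervention cohort: 60×0.75 = 45 treated and 40×0.95 = 38 untreated, so 45/83 = 54.2% treated at baseline.
- Baseline imbalance: 60.0 - 54.2 = 5.8 points.

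Analysis (b) estimates change in the same patients. If no prescribing changes, the change is 0 in both arms. Now suppose 10% of untreated patients start treatment in both arms (assumed), so that there is no true effect:

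- Change, intervention: 0.10×38/83 = 4.6 points.
- Change, control: 0.10×40% = 4.0 points.
- Spurious difference in change: about 0.6 points, in favour of the intervention.
- Post-test comparison of the same cohorts: 54.2 + 4.6 = 58.8% against 60.0 + 4.0 = 64.0%, a spurious 5.2 points against the intervention.

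If the extra visits came from treated patients instead, the imbalance would reverse: 57/(57+30) = 65.5% against 60.0%. The sign therefore depends on who returns, which the document does not tell us.

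**Analysis (a).** Let r be the share of practices retained and g the difference in the indicator, retained minus lost practices (g is assumed). The prevalence in retained practices exceeds that in all practices by (1-r)×g.

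- Within one arm, g = 10 points and r = 0.5 to 0.6: a shift of 5 to 4 points with no prescribing change.
- Between arms, equal r and equal g: bias 0.
- Between arms, r = 0.5 against 0.6 with g = 10 in both: 5 - 4 = 1 point.
- Between arms, g = 10 in one arm and 0 in the other: 4 to 5 points, against the planned 10.

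**Analysis (c).** No arithmetic is needed. By the article's own example the 6-month denominator is baseline status, before any clinical meeting. Under the general rule, which looks back 6-12 months, the denominator moves forward, so at 12 and 18 months it can rest on status that the intervention has already altered. By then the wait-control group has entered the intervention too, and no untreated contrast remains.

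**The case against.** A reader might infer that all three sets break the randomised comparison and contradict intention to treat. The document does not support that.

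- Analysis (c) is a baseline-defined subgroup in the only period with an untreated control. That it counts only gains follows from its stated aim of looking at patients with room to improve, and (a) and (b) show net change beside it.
- Analysis (a) keeps practices in their allocated groups, and repeated cross-sections are a legitimate cluster-trial design. Loss that is alike in every arm cancels between arms. It does not cancel in the before-and-after comparisons within an arm, which are also planned. Equal loss cannot be presumed either, since practices are unblinded and the groups do different work.
- Intention to treat is stated for the post-test comparison, not for (a) to (c) as such. The cohort is named for the supplementary regressions, and whether the post-test model uses it is unclear. What stands is a lack of reconciliation, not a proven contradiction. How missing data enter the model is detail an article may leave to a fuller plan.

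It is also tempting to set the 5.8 points directly against the planned 10-point effect. That figure is a baseline imbalance. It nearly vanishes in the change analysis, and in a post-test comparison it would mask benefit.

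The missing anchor date must be read with care. Figure 2 gives time frames by group and is not shown here, so the fair statement is that the text gives no date.

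Finally, practices are randomised at registration, before a baseline extract exists. A set that requires a baseline, or data at both points, therefore also selects to some degree. This stands as a limit on the remedy. It is mitigated because data cleaning was asked of all practices before the first meeting.

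**Conclusion.** The point holds for (b). Its entry rule depends on a post-randomisation visit that the intervention can influence, has no stated anchor for the wait-control group in its first six months, and is not reconciled with the intention-to-treat comparison. For (a) there is an attrition risk: within-arm prevalences can shift without any prescribing change, while the between-arm contrast is biased only if loss differs by arm. For (c) the issue arises only at 12 and 18 months.

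Bias is possible, not demonstrated. The illustrations rest on assumed visit rates, baseline prescribing, uptake and retained-minus-lost gaps, so neither size nor direction can be fixed from the document. The change is worth making because it is cheap, not because a distortion of known size has been shown.

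**What to change.** 1. **Analysis (b).** Define the cohort from baseline information only: a coded diagnosis and a visit before the practice's baseline extract. Anchor follow-up to the same scheduled extract dates in all three groups, analyse by allocated group, and say that this is the set for the intention-to-treat comparison.
2. **Outcomes in (b).** Read 6-month prescribing status from the extracted record whether or not the patient has visited since. For the blood pressure indicators, keep patients without a new reading in the set and treat the value as missing in a longitudinal model that includes their baseline data.
3. **Analysis (a).** Keep the cross-sections. Add, as a sensitivity analysis, the before-and-after change in practices present at both points, and report retention by arm, including randomised practices that never supplied a baseline extract.
4. **Analysis (c).** Keep the denominator fixed at pre-intervention baseline at every time point.

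The cost is revised wording and a re-cut of data already extracted. This assumes that the extracts, described as covering patients with the relevant conditions, hold records for patients who did not return. The downside is that including non-attenders slightly dilutes the effect estimate. The article says baseline and six-month data are already being analysed, so the sets should be settled promptly.

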The evaluation of PDGPD project uses a pragmatic cluster RCT design, where one of two interventions or control status is randomly assigned to individual practices. A pragmatic cluster-randomised trial is considered an appropriate research design in public health and educational interventions as it allows more variability in the entry criteria, reduces the impact of contamination within groups, and provides administrative convenience for implementation [39,40,57,66]. PDGPD will have access to several data points to investigate immediate and mid-term impact of the quality improvement initiative. However, several potential weaknesses in the design of PDGPD are acknowledged: first, the voluntary nature of GP participation in the cluster design where a practice [cluster] agreed to participate but not all GPs in the practice received the intervention. This may lead to dilution of the intervention effect when data from all patients seen by all GPs in the practice are analysed. The intervention is designed to encourage GPs to communicate key messages with other non-participating GPs in the practice and to welcome non-enrolled GPs to attend clinical discussion meetings within the same intervention group; further, the impact of participation rate by practice can be incorporated in the regression analysis model. Second, the cross-over design (Figure 1) where the same facilitator delivers one intervention after another in the same practice and one topic in one intervention practice and the *competing* topic in another practice carries the risk of cross-contamination; allocation of clinical topic order was done at random and facilitators were trained at focusing on discrete messages of one topic at a time. Thirdly, the wait-control group provides pre-intervention comparisons only for the first six months of the trial; for practical reasons in non-research settings (i.e. need for an intervention in exchange for participation) the control group received the intervention six months later.

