Results of this evaluation will document the impact of an intervention to align GP prescribing behaviours with practice guidelines over time in Australia. Further, the evaluation will report the extent to which practice characteristics (such as rural/urban location and total number of active patients) and patient profile, (such as age, sex, presence of co-morbidities and number of medications) may affect the likelihood of adopting these prescribing changes. The ability to adopt or adapt evidence-based programs with fidelity in general practice is an important aspect to identify feasibility, acceptability and sustainability of such programs in the future. A comprehensive suite of qualitative studies have been developed for this project to assess such issues. Details on the qualitative *evaluation* components of the PDGPD will be described elsewhere.

Finally, the PDGPD project is expected to bring the following benefits:

• Improved care and outcomes for patients with heart failure and hypertension

• Acceptable and sustainable methods to promote quality improvement activities within general practice

• Purpose-built extraction and feedback tools that can calculate complex indicators useful to monitor prescribing behaviour, promote change and enable evaluation of educational interventions

• Opportunity to refine clinical indicators to better reflect quality of clinical care and outcomes of prescribing behaviour.

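### Stepwise selection is applied to the logistic models that supply the adjusted intervention odds ratio, and neither the arm term nor the imbalance covariates are exempt

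*Protocol article*

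**What the plan says.** All of the modelling text is in the Data Analysis section of the protocol article, mostly in one paragraph.

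- It opens with predictor-finding models: "Supplementary regression analyses of the cohort will identify predictors of improved prescribing at 12 and 18 months".
- It then turns to the randomised comparison: "Post-test comparisons will be conducted between the intervention and wait-control arms using intention to treat analysis", with models that allow for clustering by Network, practice and GP.
- Separate logistic models are planned for CHF and HT, followed by: "Stepwise regression techniques will be used. Odds ratios will be used as the common measure of the estimated effect of the intervention". That last sentence goes on to use odds ratios for the explanatory variables as well.
- To deal with chance imbalance between groups, "explanatory variables for each model will include patient characteristics, practice characteristics, and location of the Network".

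Earlier in the same section, the three groups are also compared with cluster-adjusted proportions, 95% confidence intervals and chi-square statistics, without covariate selection.

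The Discussion, on dilution where only some GPs in a practice took part, adds that "the impact of participation rate by practice can be incorporated in the regression analysis model".

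**The concern.** Read in order, the sentences put the intervention effect and the covariate effects in the same models and make those models stepwise. No sentence says that the arm term stays in whatever its p-value, or that stepwise selection applies only to the predictor search. Three consequences follow if the text is carried out as written.

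1. The arm term can be selected out. There is then no adjusted estimate of the randomised effect to report, and an estimate that survives selection is on average too large.
2. The covariates meant to correct chance imbalance can be deleted on a p-value, although the plan says each model will contain them. Network matters most, because randomisation was blocked to balance practices within Networks.
3. Standard errors and confidence intervals are computed as if the final model had been chosen in advance. An odds ratio also depends on the covariates it is conditional on, so the CHF and HT odds ratios could be adjusted for different sets that nobody chose beforehand.

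At stake is the adjusted intervention odds ratio, and how far it can be called an intention-to-treat estimate.

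**Working it through.** **Inputs from the protocol article (Sample Size estimations).** ICC 0.08, 80% power, 5% significance (taken as two-sided), 86 CHF patients per practice, 99 practices over three arms (33 per arm), target differences of 10 points (ACE inhibitors) and 15 points (beta blockers). The baseline rate is not given.

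**The plan's own figure.** Design effect = 1 + (86 − 1) × 0.08 = 7.8. With an assumed baseline of 60% and a target of 70%, patients per arm without clustering, by the pooled-variance formula:

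[1.96 × √(2 × 0.65 × 0.35) + 0.842 × √(0.60 × 0.40 + 0.70 × 0.30)]² / 0.10² ≈ 356.

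Practices per arm = 356 × 7.8 / 86 = 32.3, rounded up to 33, so 3 × 33 = 99. A 30% baseline gives the same number; baselines from 20% to 85% give 39 to 108. The stated 99 is thus consistent with a 60% baseline, which is used below.

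**Simulation of selection on the arm term.** 33 versus 33 practices, 86 patients each, beta-binomial outcomes with ICC 0.08, practice-level linear model, 3,000 runs per setting. The term is kept only if p<0.05, which is an assumption because the plan gives no rule.

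| True effect | Arm forced in: mean estimate | Power | Arm dropped under selection | Mean estimate when kept |
|---|---|---|---|---|
| +10 points | +10.0 to +10.1 | 78-80% | 20-22% | +11.3 |
| +15 points | +15.1 | 99% | about 1% | +15.2 |

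A second simulation (600 runs, forward selection at p<0.05, 12 noise covariates) kept the arm term in 75.8% of trials, so dropped it in 24.2%, with retained estimates 1.14 times the truth. Together these give the range of about 20-25%.

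**Analytic check.** For an unbiased normal estimate with standardised effect δ, the mean given significance is δ + φ(δ − 1.96)/Φ(δ − 1.96), ignoring the far tail. At 80% power δ = 1.96 + 0.84 = 2.80, so the mean is 2.80 + 0.280/0.80 = 3.15. The ratio is 3.15/2.80 = 1.125, or about +11.3 for a true +10. The overstatement is therefore the ordinary significance filter, and it arises here because the arm term is itself open to selection.

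**Type I error with the arm forced in.** In the 600-run simulation, selecting only the covariates gave 6.3% null rejection. The Monte Carlo standard error is √(0.05 × 0.95/600) = 0.9 points, so the excess is (6.3 − 5.0)/0.9 ≈ 1.4 standard errors, which cannot be told from 5%. These linear simulations do not measure how the odds ratio shifts with the covariate set.

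**Participation rate.** Same 3,000-run design, true effect +10 points, participation assumed uniform on 30-100% and the effect proportional to it.

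- Rate measures receipt, so is zero in the wait-control arm: the arm coefficient goes from +10.1 to +0.1 points, power from 80% to 5%, and the standard error is 2.5 times larger.
- Rate measures GP consent, with the same distribution in both arms: the arm estimate stays at +10.0 points, with power 77% against 78%.

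**The case against.** The strongest reply is that the paragraph opens with supplementary regressions, commits to intention to treat and names its covariate classes. On that reading, stepwise selection was meant only for the predictor models, or only for covariates. That is possible, but the text does not separate the two uses, and the sentence after the stepwise statement takes the intervention effect from these models.

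A second reply is that entry rules and forced terms belong in a statistical analysis plan that is not shown. That holds for thresholds. The choice of stepwise selection is stated here, next to a covariate commitment it can undo.

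A third reply is that the inflation is no more than the significance filter, and that it does harm only if a dropped arm term goes unreported. The first part is right, as the analytic check shows. On the second, the plan does not say what is reported when the arm term is dropped.

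A reader might also infer that the plan adjusts the effect model for post-randomisation participation and so cancels the intervention effect by construction. The documents do not support that. Participation rate is absent from the Data Analysis covariate list. It appears only as an option in the Discussion, without a definition, a time of measurement or an assigned model. Talk of GPs who received the intervention suggests receipt, but the Discussion also speaks of non-enrolled GPs, and GP consent was obtained before data extraction, so an enrolment rate is equally possible. Cancellation needs a receipt-based rate entered as a main effect in the effect model.

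Nor can the medication count be called a post-treatment adjustment. The Discussion lists "presence of co-morbidities and number of medications" among patient factors that may influence uptake, with no timing given.

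**Conclusion.** The point holds for the adjusted intervention odds ratio. The plan prescribes stepwise selection for the models that supply it and protects neither the arm term nor the imbalance covariates. This fits poorly with the stated intention-to-treat aim and covariate commitment.

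If the arm term is open to selection at p<0.05, it is lost in about 20-25% of trials near the design power and overstated by roughly an eighth when kept, for a true effect of +10 points. At +15 points neither problem is material. These sizes rest on an assumed 60% baseline or, in the second simulation, on 12 assumed noise covariates, and on a practice-level linear model. They illustrate the mechanism and do not predict this trial's result.

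Three stronger conclusions are not supported: that type I error is shown to be inflated when the arm term is forced in, that participation adjustment will remove the effect, and that the whole between-arm evidence is compromised. The clustered chi-square comparisons do not depend on these models.

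**What to change.** For the intervention-versus-wait-control model, state that the arm term and a pre-specified list of baseline covariates are always included and that no stepwise selection is used. The list should contain Network (the blocking factor), the baseline value of the indicator, and named practice and patient characteristics from the classes the plan already gives.

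Confine stepwise selection to the supplementary 12- and 18-month predictor models and label them exploratory.

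Keep participation rate out of the intention-to-treat effect model. If it is studied, define it, say when it is measured, and report it as a separate secondary analysis. A rate measuring receipt would be zero in the wait-control arm for the first six months and would absorb the arm effect.

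The cost is a change of wording and model code and a small loss of flexibility in modelling. No new data are needed. The article says that baseline and six-month data are already being analysed, so the change should be dated and recorded relative to any comparison by group.
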